### Sample size

We hypothesize that two sessions of tDCS will reduce the incidence of postoperative delirium compared to the sham stimulation group. A meta-analysis published in 2023 on the incidence of delirium following non-cardiac surgeries in China reported an approximate postoperative delirium rate of 20% (24). The study by Tao et al. demonstrated that a single session of tDCS postoperatively reduced the incidence of delirium in elderly patients undergoing lower limb joint replacement under general anesthesia, decreasing it from 19.7% to 4.9% (6). Therefore, we conducted a sample size calculation based on a two-sided chi-square test, using a significance level of 0.05 and a power of 0.8, which indicated that 71 participants per group are required. Considering a 10% loss to follow-up rate observed in previous studies, the final sample size was set at 80 participants per group.

### Statistical analysis

The Kolmogorov-Smirnov test will be used to assess the normality of the data. For continuous variables that follow a normal distribution, the mean and standard deviation (SD) will be reported, while non-normally distributed variables will be expressed as median and interquartile ranges (IQRs). Independent sample *t*-tests will be used for normally distributed data, and the Mann-Whitney U test will be applied for non-normally distributed data. For the binary outcomes, chi square test or fisher exact test will be implemented.

The difference between-groups on the primary outcome will be reported as relative risk (RR) with 95% confidence intervals (CI), and the *p*-value < 0.05 will be considered statistically difference. All *p*-values for secondary outcomes and other exploratory analyses will be calculated to explore their potential impact on the overall study conclusions. These *p*-values will be considered nominal and should be interpreted as descriptive.

If patients sign the informed consent but refuse the assigned intervention, they will still be included in the statistical analysis, and patients who refuse the delirium assessment, they will be considered as having delirium. The study will use both the Intention-to-Treat (ITT) and Per-Protocol (PP) populations for statistical analysis. SPSS 26.0 (IBM Corp, Armonk NY) will be used for statistical analyses, with a 2-sided and *p*-value < 0.05 considered statistically significant.

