**Figure 1 F1:**
[figure not shown]
Trial flow chart. tDCS, transcranial direct current stimulation; ITT, intention-to-treat; PP, per-protocol.

**Table 1 T1:** Time schedule of the trial process.

**Item**	**T0**	**Pre-surgery**			**Post-surgery**						

		**f1**	**1st tDCS**	**f2**	**f3**	**2nd tDCS**	**f4**	**Day 1**	**Day 2**	**Day 3**	**Day 5**
Enrolment											
Informed consent	×										
Eligibility screen	×										
Demographics	×										
Diagnosis	×										
Comorbidities	×										
Frailty scale	×										
ASA grade	×										
MMSE	×										×
GAD-7	×							×		×	
PHQ-9	×							×		×	
Laboratory tests	×										
Randomization	×										
Interventions		×	×	×	×	×	×				
Assessments											
3D-CAM^*^	×							×	×	×	
NRS	×							×	×	×	×
Analgesia								×	×	×	
PSQI	×							×	×	×	
Complications											×

The four functional near-infrared spectroscopy (fNIRS) assessments will be conducted at specific time points before and after transcranial direct current stimulation (tDCS) as follows: (1) pre-surgery, pre-tDCS (f1): the first fNIRS measurement will be obtained prior to surgery, before the first application of tDCS; (2) pre-surgery, post first tDCS (f2): the second fNIRS measurement will be performed before surgery, following the first application of tDCS; (3) post-surgery, before second tDCS (f3): the third fNIRS measurement will be conducted after surgery, before the second application of tDCS; (4) post-surgery, post second tDCS (f4): the fourth fNIRS measurement will be taken after surgery, following the second application of tDCS. ASA, American Society of Anesthesiologists; MMSE, Mini-Mental State Examination; GAD-7, Generalized Anxiety Disorder-7; 3D-CAM, 3-min diagnostic interview for Confusion Assessment Method; PHQ-9, Patient Health Questionnaire-9; ^*^indicates twice a day, once in the morning and once in the afternoon; NRS, Numeric Rating Scale; PSQI, Pittsburgh Sleep Quality Index.

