### Data collection

#### Baseline characteristics

After enrollment, the following baseline characteristics will be recorded for each subject: age, gender, height, body mass index (BMI), years of education, and preoperative comorbidities including hypertension, coronary heart disease (with a documented history), arrhythmia (defined as sinus bradycardia, sinus arrest, atrial fibrillation, and other arrhythmias requiring medication intervention), history of stroke (including ischemic stroke and hemorrhagic stroke), obesity (defined as BMI ≥ 30 kg/m^2^), Charlson comorbidity index, ASA classification, MMSE score, frailty screening scale, anxiety and depression scores, anesthesia and surgical history. Preoperative laboratory tests will include serum albumin, hemoglobin, C-reactive protein, neutrophils/lymphocytes, and type of surgery (hip replacement, open reduction and internal fixation, or closed reduction).

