### Clinical outcomes and assessments

The primary outcome of this study is the occurrence rate of delirium on post-operative days 1, 2, and 3. Secondary outcomes include the severity of POD, pain scores at rest and during movement, anxiety and depression scores, sleep quality, as well as post-operative cognitive function and complications. Another key outcome is the change of whole brain cortical networks and brain activation patterns during resting state and verbal fluency tasks.

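### Continuous secondary scores are to be compared by a t-test or Mann-Whitney test chosen by a normality pre-test, with no stated use of the baseline or repeated values that Table 1 collects

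*Protocol article*

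**What the plan says.** The Statistical analysis section sets one rule for continuous variables. First, "The Kolmogorov-Smirnov test will be used to assess the normality of the data". Then "Independent sample *t*-tests will be used for normally distributed data", while "the Mann-Whitney U test will be applied for non-normally distributed data". The same check decides whether a variable is summarised by mean and SD or by median and IQR. No covariate, change score, ANCOVA or repeated-measures model is named.

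The Clinical outcomes and assessments section lists the variables concerned: "Secondary outcomes include the severity of POD, pain scores at rest and during movement, anxiety and depression scores, sleep quality", followed by cognitive function and complications.

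Table 1 ("Time schedule of the trial process") schedules these scores as follows:

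| Score | Baseline | Post-operative days |
|---|---|---|
| NRS pain | T0 | 1, 2, 3, 5 |
| PSQI | T0 | 1, 2, 3 |
| GAD-7, PHQ-9 | T0 | 1, 3 |
| MMSE | T0 | 5 |

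The Baseline characteristics section also lists "MMSE score, frailty screening scale, anxiety and depression scores, anesthesia and surgical history" among the data recorded at entry. No baseline is scheduled for delirium severity (DRS-R-98).

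On the standing of the secondary tests, the Statistical analysis section adds: "These *p*-values will be considered nominal and should be interpreted as descriptive".

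**The concern.** An independent-samples test takes one value per patient. It cannot use the T0 score as a covariate, and it cannot combine several days unless they are first reduced to one number. The named tests therefore leave unused much of what the schedule collects. The trial is sized only for the binary primary outcome, so precision on the secondary scores is limited to begin with.

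The gate adds a second problem. If the Kolmogorov-Smirnov test passes, the comparison is of means; if it fails, it is of ranks, and the summary statistics change with it. These are bounded, discrete scores (NRS has 11 points; GAD-7 and PSQI run from 0 to 21), so a switch is realistic. What is reported for a scale is then settled by the observed data and not in advance.

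**Working it through.** **The plan's own figure.** The only computed number is the sample size for the primary outcome: 71 per group, raised to 80. The arcsine formula for 19.7% against 4.9% gives 70.06, rounded up to 71, and 71/0.9 = 78.9, close to 80. It does not cover the secondary scores. It matters here only as the source of n: 80 less 10% leaves about 72 evaluable per arm.

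**Assumption.** The documents give no SD and no correlation for any score. The correlation rho between baseline and post-operative values is therefore assumed, over the range 0.3 to 0.7. Differences are in SD units.

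**Unadjusted, one day.** Detectable difference at 80% power, two-sided 0.05: (1.960 + 0.842) × √(2/72) = 0.467 SD.

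**Adjusted for baseline, one day.** The variance factor is 1 − rho², the CI width factor is its square root, and the equivalent unadjusted sample is 72/(1 − rho²).

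| rho | Variance factor | CI width factor | Detectable difference | Equivalent n per arm | Power at 0.467 SD |
|---|---|---|---|---|---|
| 0.3 | 0.91 | 0.95 | 0.445 SD | 79 | 84% |
| 0.5 | 0.75 | 0.87 | 0.404 SD | 96 | 90% |
| 0.7 | 0.51 | 0.71 | 0.333 SD | 141 | 97.5% |

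**Adjusted for baseline, mean of k post-operative days.** With equal correlations the variance, relative to an unadjusted single day, is [1 + (k − 1)rho]/k − rho².

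| rho | k = 2 (GAD-7, PHQ-9) | k = 3 (PSQI) |
|---|---|---|
| 0.3 | 0.65 − 0.09 = 0.56 | 0.533 − 0.09 = 0.44 |
| 0.5 | 0.75 − 0.25 = 0.50 | 0.667 − 0.25 = 0.42 |
| 0.7 | 0.85 − 0.49 = 0.36 | 0.80 − 0.49 = 0.31 |

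These factors apply to the effect averaged over days, which is a different quantity from the effect on one day. Part of the reduction comes from averaging alone; the baseline contributes the rho² term.

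**Simulation of the stated procedure.** Pre-test, then t-test or Mann-Whitney, against ANCOVA; 72 per arm, 1,500 runs per setting, true difference 0.467 SD.

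| Scores | rho | Power, stated procedure | Power, ANCOVA |
|---|---|---|---|
| Normal | 0.3 | 0.80 | 0.84 |
| Normal | 0.5 | 0.80 | 0.90 |
| Normal | 0.7 | 0.80 | 0.97 |
| Skewed, rounded | 0.3 | 0.77 | 0.75 |
| Skewed, rounded | 0.5 | 0.78 | 0.82 |
| Skewed, rounded | 0.7 | 0.77 | 0.92 |

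Simulation error near 0.77 is about √(0.77 × 0.23/1500) = 0.011, so the skewed result at rho 0.3 shows no gain and is not evidence of a loss. With no true difference, the stated procedure rejected in 0.043 to 0.057 of runs.

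**The case against.** The strongest reply is that this is an efficiency preference about descriptive outcomes in a condensed article. Randomised two-sample comparisons are unbiased without adjustment, error rates hold, the primary outcome is unaffected, and covariates or longitudinal models may be set out in an analysis plan that is not shown.

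Much of that stands, and it rules out four stronger readings that a reader might infer:

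- *That raw scores are tested separately at every visit.* The section does not say which day is tested, whether days are pooled, or whether raw or change scores are used. Visit-by-visit testing of raw scores is one possible reading. Unadjusted change scores would be another, with variance factor 2(1 − rho), worse than ignoring baseline when rho is below 0.5.
- *That there is an uncontrolled multiplicity problem.* The section already labels secondary p-values nominal and descriptive.
- *That day-5 MMSE mostly reflects the starting value.* This would need rho² above 0.5, so rho above 0.71, which nothing in the documents supports.
- *That every scale gains much.* Nothing shows that the scales share one correlation, and the skewed case at 0.3 shows no gain.

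What does not stand is the appeal to an unseen plan. The article names the tests and the rule for choosing between them, so this is a stated choice and not an omitted detail. Descriptive status also does not remove the cost: a descriptive result still needs a precise estimate on a scale fixed beforehand.

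**Conclusion.** The point holds as one of precision and consistency for the continuous secondary scores only. At assumed correlations of 0.3 to 0.7, leaving out the baseline forgoes 9% to 49% of the variance of a single-day comparison of roughly normal scores. For skewed scores the benefit is absent at about 0.3 and clear at 0.7. Further precision is available for day-averaged effects on NRS, PSQI, GAD-7 and PHQ-9; MMSE, with one post-operative value, can gain from baseline adjustment alone. Separately, the pre-test leaves the choice between a mean difference and a rank comparison to the data. All sizes rest on correlations that the documents do not give, and the day-averaged figures also on equal correlations. The change is recommended rather than essential.

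**What to change.** In the Statistical analysis section, before unblinding:

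- **MMSE, day 5:** ANCOVA with arm and T0 MMSE.
- **NRS, PSQI, GAD-7 and PHQ-9:** for each score, a mixed model with arm, day, arm-by-day and the T0 score, over the days in Table 1. State whether the reported contrast is averaged over days or for a named day; the gain from repeated values applies to the averaged contrast.
- **Reporting:** adjusted mean differences with 95% CI, using robust or bootstrap standard errors if scores are skewed.
- **Test choice:** stop using the Kolmogorov-Smirnov result to choose the test, and keep Mann-Whitney as a sensitivity analysis.

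Delirium severity on the DRS-R-98 has no scheduled baseline and is not covered by this change. The cost is wording: the scores are already scheduled, no patients are added, and SPSS 26.0, the package named in the plan, fits these models.

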## Discussion

This randomized, double-blind, single center clinical trial investigates the effects of tDCS on POD in elderly patients undergoing hip fracture surgery under spinal anesthesia. Compared to sham stimulation, active tDCS is expected to effectively reduce the incidence and severity of POD while enhancing frontal cortical activity. Previous studies have demonstrated that tDCS can improve cognitive function in post-stroke patients, enhancing working memory, attention, and daily activity performance (25, 26). This study will provide theoretical support for the clinical application of tDCS and offer a safe and effective strategy for the prevention or early intervention of delirium.

fNIRS is used to explore the mechanisms underlying POD, which contains the following features: (1) simplicity and versatility: fNIRS is a simple, portable, and highly adaptable tool that has been widely applied in stroke rehabilitation, motor function studies, learning, and mental health research (27); (2) naturalistic monitoring: fNIRS enables researchers to monitor brain activity under simulated real-world conditions, allowing participants to perform cognitive tasks and resting state imaging in an open, patient-friendly, and clinical care environment (28); (3) safety and cost-effectiveness: fNIRS is a safe and relatively inexpensive imaging technique. Compared to other neuroimaging modalities, such as functional magnetic resonance imaging (fMRI), it offers superior temporal resolution and is well-suited for studying of dynamic brain activity (29).

In summary, this study highlights the potential of tDCS as an effective and safe intervention for reducing POD in elderly patients undergoing hip fracture surgery. By integrating fNIRS imaging, the research provides novel insights into the neural mechanisms underlying POD and contributes to the development of innovative rehabilitation strategies. Future multicenter trials with larger sample sizes are recommended to validate these findings and explore the broader applicability of this intervention.
